2.2.2 Diagnosis of IGT and prediction of diabetes. IGT is quantitatively a major problem.  The prevalence increases with age, and, by WHO criteria, reaches 23% at ages 65‑74 years in the U.S. population according to the National Health and Nutritional Examination Survey (Harris, et al, 1987). Several population studies have shown people with IGT to be at increased risk of developing diabetes, although if their glucose tolerance does not deteriorate, they are not at risk of diabetic complications.  There is, however, evidence that they are at increased risk of coronary disease (Fuller, et al, 1980).  There have been at least eleven studies of the rate at which persons with IGT progress to overt diabetes. These studies, summarized in Table 2.1, are difficult to compare because different diagnostic criteria for IGT and diabetes have been used, differing especially for IGT. Most of these predated the WHO criteria (World Health Organization, 1985) for glucose tolerance and used criteria which are much less stringent, i.e. they included many subjects who would be normal by WHO criteria. Thus in those studies using WHO criteria, such as the studies in Malmöhus County (in a subset of subjects meeting WHO criteria for IGT), Nauru, Malmö, Malta, San Antonio, and the Pima Indian study, the incidence rates of diabetes were higher, at 19-61% in 5-10 years. In the others, the two-hour blood glucose at entry was consistently a strong predictor of future diabetes, so it is reasonable to estimate that had the more stringent WHO criteria been used, the incidence rates might have been higher and similar to those in the studies in which WHO criteria were used. The best estimates of incidence rates to be anticipated in subjects with IGT by WHO criteria are based on those studies shown in Table 2.1 in which WHO criteria were used.

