2.3 JUSTIFICATION FOR THE PRESENT STUDY

2.3.1 Justification of the study design. Because the question of whether diabetes can be prevented in subjects with IGT is so important but not yet clearly answered, we propose a new clinical trial to test the hypothesis.  The efficacy of diet-exercise program will be tested. There are several reasons for suspecting these treatments may be effective.  Among those with IGT, obesity, the degree of hyperglycemia, insulin resistance, and impaired insulin secretion have been identified as major risk factors for type 2 diabetes.  Thus therapeutic measures designed to reduce body weight and hyperglycemia might be effective in preventing the deteriora­tion of IGT to diabetes. This study will test a diet-exercise treatment program including exercise and a diet designed to imporove hyperglycemia and reduce body weight.

Diabetes and insulin resistance are now commonly agreed to increase the risk of CHD and stroke ( Pyörälä et al. 1983, Black 1990) over and above the other major cardiovascular risk factors. It is not known whether this excess risk could be reduced by preventing the worsening of glugose intolerance. Recently, developments in high-resolution B-mode ultrasound has made it possible to quantify mild and moderate asymptomatic lesion formation and also to monitor serial arterial change ( Pignoli et al 1986, Bond et al 1991, Riley et al 1991). Preliminary population based data from the large ARIC study in the US (the ARIC Investigators 1989) show that diabetic sujects had significantly larger carotic artery wall thicness even when stratifying for smoking, hypertension and hypercholesterolemia (Chambless et al 1992, unpublished data). As the secondary hypothesis our study will test whether the prevention of worsening of glucose intolerance will prevent atherosclerosis and/or acute CVD events.

Physical activity

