3.5 REGISTRATION, RANDOMIZATION, AND STRATIFICATION

3.5.1 Treatment assignment and registration. Assignment will be issued by the Clinical Center which will register enrollment of subjects upon verification that all eligibility criteria have been met.

3.5.2 Randomization to treatment. Subjects will be randomly allocated to special or standard diet-exercise program in the following way:

Group 1: Special diet - exercise

Group 2: Standard diet - exercise

3.5.3 Stratification. Randomization will be stratified by 1) Clinical Center and 2) the 2-hour post-load glucose obtained during the OGTT:

o Stratum 1: venous plasma glucose = 7.8-9.4 mM (140-169 mg/dl)

o Stratum 2: venous plasma glucose = 9.5-11.0 mM (170-199 mg/dl)

3.5.4 Registration. Subjects are enrolled in the DPS as soon as they are registered by the Clinical Center. The Clinical Center will promptly register a subject upon verification that all eligibility criteria have been met. A registration number (and treatment assignment) is given to the subject according to the randomization list.

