8.2 PRETREATMENT CHARACTERISTICS

An analysis of pretreatment characteristics of enrolled subjects, by Clinical Center and by assigned treatment, will be undertaken in order to provide descriptions of the population studied and to determine whether stratified randomization succeeded in balancing the various treatment groups with respect to potential risk factors for diabetes. In the unlikely event that such balance is not achieved, methods of covariate adjustment, such as standardization of rates or the Cox proportional hazards model will be used.

The pretreatment characteristics to be analyzed include:

o age, sex, ethnicity

o physical fitness

o physical activity

o waist and hip circumference, waist-hip ratio

o sagittal and transverse diameters

o height, weight, body mass index

o lean body mass

o systolic and diastolic blood pressure, hypertension

o cigarette smoking

o dietary intake

o laboratory measurements (plasma glucose and lipids, serum creatinine, c-peptide, and insulin)

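### Section 8.2 makes covariate adjustment of the diabetes comparison depend on observed baseline imbalance, with no criterion, covariates or primary result fixed; adjust in every case for named predictors instead

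*Protocol*

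**What the plan says.** Section 8.2 analyses pretreatment characteristics by center and by arm, partly "to determine whether stratified randomization succeeded in balancing the various treatment groups with respect to potential risk factors for diabetes". It then sets a condition: "In the unlikely event that such balance is not achieved, methods of covariate adjustment" are brought in. No threshold for imbalance is given, and no covariates are named. Two methods, rate standardization and a Cox model, are offered as examples. The section does not say whether an adjusted result replaces the crude one or stands beside it.

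The list that follows is open ("The pretreatment characteristics to be analyzed include") and ends with "laboratory measurements (plasma glucose and lipids, serum creatinine, c-peptide, and insulin").

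Section 3.5.3 says what design controls: "Randomization will be stratified by 1) Clinical Center and 2) the 2-hour post-load glucose obtained during the OGTT", the latter in two strata.

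Section 8.3.1 analyses cumulative incidence by treatment group with the life-table method and names no covariates. The multivariate models of section 8.4 come in addition to the treatment comparison and serve prognosis, so they do not fix an adjusted comparison.

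The protocol already names strong predictors. Section 2.2.2 says "the two-hour blood glucose at entry was consistently a strong predictor of future diabetes". Section 2.3.1 says that obesity, hyperglycemia, insulin resistance and impaired insulin secretion "have been identified as major risk factors for type 2 diabetes".

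**The concern.** A rule that turns adjustment on only after a balance check has two faults.

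First, someone must decide, with the arms in view, what counts as imbalance, which covariates enter and by which method. That is discretion over how the diabetes comparison is made.

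Second, chance imbalance is unrelated to how strongly a variable predicts diabetes. A strong predictor that happens to be balanced stays out of the model and its precision gain is lost. A weak predictor that happens to be imbalanced goes in to little purpose.

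Calling imbalance unlikely hides both faults, because it suggests that the rule will hardly ever be used. This is not a detail left to a later analysis plan: the protocol states the rule, and an analysis plan would have to follow it or contradict it.

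**Working it through.** **The plan's own figure.** Section 8.2 gives no number, only the word unlikely. The sample size matters for what follows and reproduces. With p1 = 0.28, p2 = 0.175, mean 0.2275, two-sided 5% and 80% power, the section 3.8 formula gives 249.05, rounded up to 250 per arm, so 2N = 500. Then 500/0.90 = 556, about 560, or 280 per arm.

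**Counting the list in 8.2.** Age, sex, ethnicity (3); fitness (1); activity (1); waist, hip, ratio (3); two diameters (2); height, weight, BMI (3); lean mass (1); systolic pressure, diastolic pressure, hypertension (3); smoking (1); diet (1); glucose, lipids, creatinine, c-peptide, insulin (5). Sum: 3+1+1+3+2+3+1+3+1+1+5 = 24.

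**Chance of at least one imbalance.** The protocol gives no cut-off, so each cut-off here is an assumption. For independent items the probability is 1 − (1 − a)^24. For a standardized difference d, the standard error is √(2/280) = 0.0845 and a = 2[1 − Φ(d/0.0845)].

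| Cut-off per item | a | P(at least one of 24) |
|---|---|---|
| 10% test | 0.10 | 92% |
| 5% test | 0.05 | 71% |
| 1% test | 0.01 | 21% |
| d > 0.10 | 0.237 | 99.8% |
| d > 0.15 | 0.076 | 85% |
| d > 0.20 | 0.018 | 35% |
| d > 0.25 | 0.003 | 7% |

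At the 5% test, leaving out one item as controlled by stratification gives 1 − 0.95^23 = 69%. The items are not independent, so the 5% case was repeated with 200,000 simulated draws:

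- Correlation within related blocks of 0.3, 0.5, 0.7 and 0.9: 68%, 65%, 60% and 52%.
- A common correlation across all 24 of 0.3 and 0.5: 59% and 46%.

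**Does the trigger find the predictors that matter?** At 5%, any one unstratified predictor is flagged about 5% of the time, and at least one of three 1 − 0.95³ = 14% of the time. Two-hour glucose, being stratified, would be flagged less often.

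**Power.** The simulation used 560 subjects, 24 independent covariates, 28% control incidence at 5 years, a Cox model and 2,500 trials per row. The hazard ratio was ln(0.804)/ln(0.72) = 0.664, which corresponds to the 28% to 19.6% stated in section 3.8. It was applied conditionally on the predictors, so treated incidence came out at about 20% (19.9-20.5%). Under the rule, only items flagged at 5% were adjusted for. The log hazard ratios per SD are assumptions; the documents give none.

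| Assumed log HR per SD | Unadjusted | Rule | Always adjusted | Gain over rule |
|---|---|---|---|---|
| 0.5 | 62.1% | 61.9% | 65.0% | about 3 points |
| 0.5, 0.4, 0.3 | 60.0% | 60.4% | 66.2% | about 6 points |
| 0.7, 0.5, 0.3 | 55.8% | 56.1% | 65.3% | about 9 points |

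The Monte Carlo standard error of each power is about √(0.6×0.4/2500) = 1 point. The trigger fired in 69-71% of trials, but on a prognostic covariate in only 5-15%, so the rule performs much like no adjustment.

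A second simulation used the 17.5% treated rate that section 3.8 puts into its formula. With log hazard ratios of 0.6/0.3/0.3 and 0.8/0.4/0.4, power was 78.9% under the rule and 83.4% always adjusted, then 74.6% and 83.6%. The gains are 4.5 and 9.0 points.

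**Type I error.** In the first simulation the rule rejected in 4.2-4.6% of null trials and pre-specified adjustment in 4.1-4.6%. Picking the more favourable of the crude and triggered results gave 4.9-5.5%. In the second simulation overall size was 4.5-5.6% for every strategy.

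**The case against.** The protocol never says that each of 24 items is tested at 5%. It speaks of balance on potential risk factors for diabetes, and the list includes items such as height and creatinine that few would act on. Under a stricter cut-off, or strong common correlation, imbalance is less likely than not. This stands: more likely than not is true under one common convention only. But probabilities from 7% to 99.8%, depending on an unstated cut-off, show that the rule cannot be applied without a later choice.

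Section 8.2 also does not say that only imbalanced items would enter the model, or that the adjusted result would replace the life table in 8.3.1. An adjusted result reported as supplementary is a fair reading. This stands too. The power figures hold only if adjustment is limited to flagged items or is not used. The text settles neither question, and that is the gap.

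A reader might infer that the rule inflates false positives. The documents and the checks do not support that. Among null trials where the main predictor just misses the trigger, unadjusted rejection of 7-8% can be found, but that is conditional on a chosen band and treats the predictor as unstratified. Two-hour glucose, which the protocol calls a strong predictor, is stratified. Overall size stays near 5%.

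Finally, a gain of a few points is an efficiency matter and does not make the planned analysis invalid. That is fair, and it limits the severity.

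**Conclusion.** The point holds in this form: section 8.2 makes adjustment of the diabetes comparison conditional on observed imbalance, without a criterion, covariates or a primary result, and calls the trigger unlikely without support. With 24 items, at least one chance imbalance has probability 71% (independent) or 52-68% (within-block correlation 0.3-0.9) at an assumed 5% test per item. It is 46% with a common correlation of 0.5, 35% at a standardized difference above 0.20 and 21% at the 1% level.

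Imbalance is the wrong basis for choosing covariates whichever cut-off is used. The harm is discretion after the arms are seen, and a power loss of about 3 to 9 points that rests on assumed predictor strengths and on adjustment being limited to flagged items. Two stronger inferences are not supported: that adjustment will almost certainly be triggered, and that the type I error is compromised. The change is worth making because it is cheap and the main predictors are already measured; the trial remains valid without it.

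**What to change.** In sections 8.2 and 8.3.1, delete the imbalance trigger. State that the primary treatment comparison for diabetes is, in every case, one pre-specified proportional-hazards model with:

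- Clinical Center and the 2-hour glucose stratum, as strata or covariates;
- a short fixed list of predictors already collected: continuous 2-hour glucose, fasting glucose, BMI, age and sex.

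Define the 2-hour value so that it exists for everyone. A mean of two tests does not: section 5.1.1 admits subjects by routes b and c on one OGTT, and section 5.2.3 lets the first screening test use capillary blood. One defined test, such as the qualifying OGTT, with its specimen type recorded, avoids this.

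Report the crude life table beside the model, and keep the baseline table as description that plays no part in choosing the model.

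The cost is a sentence or two and no new data. The downside is that the adjusted hazard ratio is conditional on the covariates and will differ from the crude ratio, so both should be labelled.

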8.3 OUTCOME VARIABLES

8.3.1 Events. The primary outcome variable is the incidence of diabetes. Other events of interest are defined in Chapter 7. The cumulative incidence of events, by treatment group and, to evaluate prognostic factors, by subgroups determined by pre-randomization characteristics such as those listed in Section 5.3.2, will be analyzed in 1-year follow-up intervals by the lifetable method.

8.3.2 Continuous variables. Mean changes in the following variables, by treatment group and subgroups defined by pre-randomization characteristics, will be analyzed in 1-year follow-up intervals:

o systolic and diastolic blood pressure

o waist-hip ratio; waist and hip circumference

o sagittal and transverse diameters

o body mass index

o lean body mass

o GTT

o serum cholesterol

o serum triglycerides

o serum creatinine

o plasma glucose

o plasma insulin

o serum c-peptide

o glycosylated hemoglobin

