3.8 SAMPLE SIZE AND ENROLLMENT GOAL

We begin sample size determination by estimating the 5-year incidence of diabetes in the untreated persons with IGT to be 28% (see Chapter 2). Because of the uncertainty in the data needed to make this estimate, this figure may be an underestimate of the incidence of diabetes. If so, the power of the study would be greater than the following computations indicate. We are designing the study to be large enough to be able to detect, with 80% power (beta = 20%) at the 2-tailed 5% significance level (alpha = 5%), a 30% reduction in diabetes incidence due to diet-exercise treatment, ie, a reduction from 28% to 19.6%.

The possibility of a reduction in diabetes incidence by at least 30% is suggested by the results of the Malmöhus study (Sartor, et al, 1980) analyzed in accordance with randomized treatment assignment and by the nonrandomized treatment study of Eriksson and Lindgärde (1991). We are assuming that noncompliance in the DPS will be no worse than in these previous studies; therefore we are making no further adjustment for noncompliance. We will, however incorporate an adjustment for losses to follow-up, including deaths.

Letting p1 and p2 denote, respectively, the proportion of events (incidence of diabetes) in the control and treated groups, respectively, then, according to Halperin, et al (1968), the sample size required in each of the two groups is

N = {Zα[2p(1 - p)]1/2 + Zß[p1(1 - p1) + p2(1 - p2)]1/2}2 / [p1 -p2]2,

where p = (p1 + p2)/2 and Zα and Zß are the normal deviates associated with α and ß. With p1 = .28, p2 = .175, α (2-tailed) = .05, and ß = .20, the total minimum required sample size becomes

2N = 500.

In Malmöhus County from 1962-87, the mortality rate among persons aged 45-64 with IGT by WHO criteria was 19/1000 persons per year (Knowler, et al, in preparation), yielding an estimated 5.5-year cumulatie mortality rate of 10% in study participants. Allowing for 10% losses to follow-up from deaths over a 5.5-year period increases the sample size to

2N = 500/(1 - .10) = 556, or approximately 560.

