5.2 SCREENING FOR IGT

5.2.1 Population selected for screening. Cases of IGT to be studied will be found by population screening. The type of population screened will vary from one Clinical Center to another; some will select a sample representative of the general population while others will select subjects thought to be at high risk of IGT (eg, subjects who are obese, have hypertension, or have relatives with type 2 diabetes).

5.2.2 Conditions for the screening examination. Prior to the screening examination, any acute intercurrent illness or injury must be resolved and treatment of any chronic condition (such as hypertension, arthritis or hyperlipidemia) must be stabilized so that the test is performed under stable conditions.

5.2.3 The oral glucose tolerance test.

The OGTT should be administered in the morning after at least three days of unrestricted diet and usual physical activity. The test should be preceded by an overnight fast of 10-16 hours, during which water may be drunk. Smoking is not permitted during the test. The presence of factors that influence interpretation of the results of the test must be recorded (e.g., medications, inactivity, infection, etc.). In the first screening OGTT blood glucose may be analysed from capillary whole blood with a Hemocue-analyser, which is fast, easy, cheap, and yet reliable method in blood glucose screening.

After collection of the fasting venous blood sample (or capillary blood sample in the first OGTT), the subject should drink 75 g of anhydrous glucose (or partial hydrolysates of starch of the equivalent carbohydrate content or 82.5 g glucose monohydrate) in 250-300 ml of water over the course of 5 minutes. Venous (or capillary) blood samples will be collected at 1 and 2 hours after the test load (only at 2 hours in the first screening OGTT).

The blood sample should be collected in a tube containing NaF and centrifuged within 15 minutes to separate the plasma; the plasma should be kept at 4oC up to 12 hours or frozen until the glucose concentration is measured. In addition, at fasting a blood sample will be collected in a tube containing EDTA for measurement of HbA1c by high pressure liquid chromatography (HPLC).

Subjects with previously known IGT can be tested by this proce­dure to determine if they still have IGT, but must be excluded if they have been actively treated for IGT (see Section 5.1.2).

The test will be interpreted and acted on as follows:

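### The default comparison of diabetes incidence leaves out the centre and 2-hour-glucose strata used to randomize, so a little precision may go uncollected

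*Protocol*

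**What the plan says.** - Section 3.5.3: "Randomization will be stratified by 1) Clinical Center and 2) the 2-hour post-load glucose obtained during the OGTT". The two bands are 7.8-9.4 and 9.5-11.0 mM.
- Section 8.3.1: cumulative incidence of diabetes and other events, by treatment group, "will be analyzed in 1-year follow-up intervals by the lifetable method". Subgroups on pre-randomization characteristics are added to evaluate prognosis. No strata enter the arm comparison.
- Section 8.2: baseline characteristics are tabulated to see whether stratified randomization produced balance. Then: "In the unlikely event that such balance is not achieved, methods of covariate adjustment", with standardized rates or a Cox model as examples. No threshold for imbalance is set. Plasma glucose is among the listed characteristics; centre is only an axis of tabulation.
- Section 8.4: the logistic and proportional hazards models serve clinical course and prognosis.
- On prognostic strength, section 2.2.2 says that "the two-hour blood glucose at entry was consistently a strong predictor of future diabetes", section 2.3.1 counts degree of hyperglycemia among the major risk factors within IGT, and section 5.2.1 says "The type of population screened will vary from one Clinical Center to another".

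**The concern.** Stratified randomization forces the arms to agree on centre and glucose band. If those factors predict diabetes, the arm difference varies less than an unstratified standard error assumes. The test then rejects less often than its nominal 5%, and the interval is wider than it need be.

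A later analysis plan might settle the test, so silence alone would be no finding. But section 8.2 states a rule: adjust only after imbalance is seen. For the stratification factors that trigger is designed not to fire, so the default is an analysis without them. If it does fire, on some other covariate, the model for the primary endpoint is chosen after looking at baseline data, with neither threshold nor method fixed.

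**Working it through.** **Inputs from the protocol (section 3.8):** "With p1 = .28, p2 = .175", two-sided alpha 0.05, power 0.80, 10% losses.

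**Assumptions, not in the documents:** ratio of diabetes risk or hazard between glucose bands; share of subjects in the upper band (30-50%); five centres (section 3.1.4 says only several); spread of log-hazard between centres; blocks of four.

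**1. The plan's own figure.** With p = (0.28 + 0.175)/2 = 0.2275:

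N = {1.96√(2 × 0.2275 × 0.7725) + 0.8416√(0.28 × 0.72 + 0.175 × 0.825)}² / 0.105² = (1.1620 + 0.4950)² / 0.011025 = 249.05, so 250 per arm and 2N = 500. Then 500/0.9 = 556. Both reproduce. The formula has no stratum term.

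**2. Variance with and without the glucose band, 250 per arm.** With share s in the upper band and risk ratio r, the lower-band risk in each arm is p/(sr + 1 − s).

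- Unstratified: Vu = 0.28 × 0.72 + 0.175 × 0.825 = 0.3460.
- Stratified: Vs = the same sum taken within each band, weighted by share.

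Example, r = 2 and s = 0.5: control risks 18.67% and 37.33%, treated 11.67% and 23.33%.

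- Vs = 0.5(0.1518 + 0.1031) + 0.5(0.2340 + 0.1789) = 0.3339, and √(Vu/Vs) = 1.018.
- Unstratified power = Φ[(0.105 − 1.96 × 0.03720)/0.03654] = Φ(0.878) = 81.0%.
- Stratified power = Φ(0.105/0.03654 − 1.96) = Φ(0.913) = 81.9%.
- Approximate true size of the unstratified test = 2[1 − Φ(1.96 × 1.018)] = 4.6%.

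| Risk ratio | SE ratio | Power unstratified | Power stratified | Gain (points) | Size, unstratified |
|---|---|---|---|---|---|
| 1.5 | 1.006 | 80.7% | 81.1% | 0.3 | 4.9% |
| 2 | 1.018-1.020 | 81.0-81.1% | 81.9-82.1% | 0.9-1.1 | 4.6% |
| 3 | 1.042-1.056 | 81.6-81.9% | 83.7-84.6% | 2.1-2.8 | 3.9-4.1% |
| 4 | 1.062-1.094 | 82.0-82.7% | 85.0-87.1% | 3.0-4.3 | 3.2-3.7% |

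These are risk ratios. A hazard ratio of 3 with equal bands is milder: if x is lower-band five-year survival, x + x³ = 2 × 0.72 = 1.44 gives x ≈ 0.842, so risks of about 15.8% and 40.2%, a risk ratio of about 2.55.

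**3. Simulated annual-interval log-rank**, 500 subjects, five centres, blocks of four, 2,500 trials per setting, stratified by centre × glucose band:

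| Hazard ratio, centre SD | Power unstratified / stratified | Size unstratified / stratified |
|---|---|---|
| 1, 0 | 79.5% / 79.3% | 4.6% / 4.7% |
| 1.5, 0.2 | 80.0% / 80.3% | 4.2% / 4.4% |
| 2, 0 | 80.9% / 81.3% | 5.3% / 5.6% |
| 2, 0.2 | 81.3% / 82.0% | 3.6% / 4.0% |
| 3, 0.3 | 81.4% / 83.5% | 3.8% / 4.8% |

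Monte Carlo standard errors are about √(0.05 × 0.95/2500) = 0.4 point for size and √(0.8 × 0.2/2500) = 0.8 point for power. Both tests use the same simulated trials, so their difference is better determined than either figure alone.

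Repeats with 560 subjects gave gains of 0.1-0.6 points (hazard ratio 1.5, SD 0.2), 0.9-1.1 (2, 0.3), 1.3-2.5 (2.5, 0.4) and 2.2 (3, 0.4). One batch of 1,500 trials reached 3.4 points at its upper end; the other batches, at settings as strong or stronger, did not exceed 2.5.

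**4. At the other target in section 3.8.** The text of 3.8 also states 19.6% in the treated arm. There the SE ratios barely change (1.007, 1.019-1.021 and 1.043-1.058 at risk ratios 1.5, 2 and 3). Power at 250 per arm is only about 60%, and the gains become 0.5, 1.4-1.6 and 3.2-4.3 points.

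**The case against.** - **No test is named.** Section 8.3.1 gives neither a test nor a variance estimator, and a stratified log-rank would be compatible with it. A reader might infer that the protocol prescribes unstratified standard errors; it does not say so. What remains is the adjustment rule of 8.2, which a stratified primary analysis would have to depart from.
- **The prognostic evidence is thinner than the quotes suggest.** The sentence in 2.2.2 concerns studies whose criteria for IGT were wider than WHO's, so it does not give the contrast between the two bands. Section 5.2.1 concerns risk of having IGT, not of progressing once enrolled. Section 2.3.1 supports some effect of glycemia within IGT, of unknown size; no centre effect on progression is documented.
- **Planned power is intact.** A reader might infer that the trial falls short of 80% for this reason. Section 3.8 already uses the unstratified variance, so the loss is only relative to a better analysis.
- **The direction for the whole trial is not certain.** Under section 5.1.2 a spouse takes the partner's arm without separate randomization. Positive correlation within couples can make ordinary error bars too narrow, and a stratified log-rank would still treat spouses as independent. A flat statement that the trial's error bars are too wide is therefore not supported.

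All four points limit the claim. None is a reason to leave the strata out.

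**Conclusion.** The point holds as a modest matter of efficiency. The strata used to randomize are not part of the default arm comparison, and the adjustment rule of 8.2 is unlikely to bring them in. If they predict diabetes, an unstratified analysis is slightly conservative: about 0 to 2.5 power points at assumed hazard ratios of 1.5 to 3 and the 28% and 17.5% of the formula, with true size between about 3.5% and 5%. At the mild end nothing measurable is lost. The size rests wholly on assumed stratum and centre effects.

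Validity is not threatened by this, since any error it causes is on the cautious side. Two other matters are separate: clustering of spouses, and the 19.6% versus 17.5% conflict in section 3.8. The latter is far larger, since the same formula at 19.6% needs 806 evaluable subjects against 500. This point is a free or cheap improvement.

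**What to change.** In section 8.3.1, state that the primary arm comparison is stratified by, or adjusted for, Clinical Center and the two glucose bands as recorded at randomization, whatever the observed balance. One form is a stratified log-rank test on the 1-year intervals, with a stratified rate ratio and 95% confidence interval. Keep the life-table curves by arm as description. Merge very small centres by a rule fixed before outcomes are seen. In section 8.2, limit imbalance-triggered adjustment to sensitivity analysis.

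The cost is wording only, with no new data. A little information is lost in strata with few events, which the merging rule contains.
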